### Trial Management Protocols

Two named principle investigators (PI) will be recruited at each study site. Together they shall provide blinded wound reviews for the other PI's patients by being unaware of which arm of the study these patients belong to. The two wound reviews will occur firstly prior to discharge at day 5 to 7 post-operation and then a formal outpatient appointment or ward attendance for wound review will be arranged at or just after 30 days (day 30-33 post-operation). At this visit patients will also be asked to complete a retrospective questionnaire regarding their wound and its healing over the intervening period. This will ensure that full information is gathered about any wound infections, together with resulting treatment or hospital admissions, occurring between the day 5-7 and day 30-33 reviews. Enrolled patients will also be given contact details for the local primary investigator should any concerns by raised by the patient. Wound assessment at both stages will utilise a standardised proforma. These wound assessment tools will be pre-validated for reproducibility and ease-of-use in a pilot study to be ran prior to full trial launch.

QOL data will be assessed using the EQ-5D pre-operatively, at 5-7 days, at the 30-33 day follow-up visit.

We also envisage the involvement of clinical nurse specialists at most sites. Their clinic appointments are generally more accessible and it may be feasible to utilise these for the second formal (outpatient) wound review. Clinical nurse specialists are generally experienced in assessing post-operative wounds themselves and they may also therefore provide a second-line cohort of blinded wound reviewers if the relevant PI is not available.

### Study Process

Data will be recorded on a number of case report forms which are detailed in Additional file 3 Appendix 2. Figure 1 gives an overview of the study process.

**Figure 1 F1:**
[figure not shown]
**Flowchart Illustrating Study Process**.

1. Informed consent for participation in the study is obtained preoperatively, ideally at the same setting where (normal) consent for the intended surgical procedure is obtained > 24 hrs prior to surgery (except in an emergency setting). Patients will ideally have been previously given a patient information sheet at the time of listing for their operation.

2. After induction of anaesthesia at the time of surgery the patient is allocated to either the wound-edge protector group or the control (no protector) group by the surgeon, using a secure 24 hour internet-based randomisation service - provided by the UKCRC Accredited Primary Care Clinical Trials Unit, University of Birmingham.

3. Normal local policy for systemic antibiotic prophylaxis is followed.

4. Standard routine skin preparation is undertaken according to local policy.

5. Antiseptic-soaked towels on wound edges may also be used in either group.

6. The operation is carried out as normal, with removal of the wound guard (if applicable) as late as possible prior to wound closure.

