### Secondary Outcomes

Comparisons will be made to assess the impact of treatment relating to the following outcomes:

1) The degree of wound contamination (e.g. colorectal resections/vascular surgery)

2) Presence of major comorbidity (e.g. diabetes, obesity, smoking)

3) Health-related quality of life (QoL) to be assessed using the EQ-5D questionnaire

4) Length of stay in hospital

5) Health care utilisation and the incremental cost-effectiveness of the use of the wound-edge protection device compared to standard care

6) Adverse events

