### Randomisation

The most important factor in determining risk of SSI is the type of surgery performed via the laparotomy wound and resulting degree of contamination. The standard categorisation and corresponding normal infection rates [18] are shown in table 3.

**Table 3 T3:** Classification of potential surgical contamination

Type of Surgery	Examples	**Normal Infection Rate (%) **[18]
Clean (no viscus opened)	Adhesiolysis	1-2

Clean-contaminated (viscus opened, minimal spillage)	Right Hemicolectomy, Open Cholecystectomy	< 10

Contaminated (open viscus with spillage or inflammatory disease)	Colectomy with some spillage Resection of active Crohns disease	15-20

Dirty (pus or perforation, or incision through an abscess)	Diverticular perforation	< 40

Randomisation will therefore be stratified according to degree of contamination using a minimisation procedure following the methods proposed by Pocock and Simon (1975) [19] using a programme developed by [name], University of Birmingham.

Please refer to the randomisation notepad (Additional file 1 Table S1) for details of operation-specific information to be collected prior to randomisation.

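### Table 3 grades contamination partly by findings at operation, but allocation comes before the operation, so the text should say that the stratifier and the subgroup variable are the expected class

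*Protocol article*

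**What the plan says.** In the protocol article, the Randomisation section gives as its reason for stratifying that the main determinant of infection risk is "the type of surgery performed via the laparotomy wound and resulting degree of contamination". It then states: "Randomisation will therefore be stratified according to degree of contamination using a minimisation procedure". Table 3 supplies the classes. The second is "Clean-contaminated (viscus opened, minimal spillage" and the third is "Contaminated (open viscus with spillage or inflammatory disease". The first requires that no viscus is opened, and the fourth turns on pus, perforation or an abscess in the line of incision.

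The numbered steps of the Study Process fix the timing. Step 2 reads "After induction of anaesthesia at the time of surgery the patient is allocated" to the device or the control group, and it is the surgeon who does this through the web service. Skin preparation is step 4. Step 6 is the surgery: "The operation is carried out as normal, with removal of the wound guard (if applicable) as late as possible prior to wound closure".

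Contamination returns as an analysis variable. Secondary outcome 1 is "The degree of wound contamination (e.g. colorectal resections/vascular surgery", and the abstract gives as a secondary aim how contamination affects the efficacy of the device.

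**The concern.** A minimisation factor must be known when the patient is allocated. The boundary between clean-contaminated and contaminated depends on spillage, which cannot be known before the abdomen is opened. As written, the definition and the timing do not fit.

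More is at stake in the subgroup than in the allocation. Minimisation can only use what is entered at step 2, so the procedure forces some form of anticipated class. Secondary outcome 1 has no such safeguard. It could be run on the anticipated class or on a class assigned after the operation. The second would be a post-randomisation variable. The surgeon performs the allocation and sees the device in the wound, and the blinding described under Trial Management Protocols covers the later wound reviews, not judgements made in theatre. The question matters because the Background reports earlier reductions of up to 84% that varied with wound contamination.

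**Working it through.** **1. Order of events against definitions**

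| Class (Table 3) | What decides it | Known at step 2? |
|---|---|---|
| Clean | No viscus opened | Often predictable (planned adhesiolysis), not certain |
| Clean-contaminated | Viscus opened, little spillage | Opening often planned; spillage not known |
| Contaminated | Spillage, or inflammatory disease | Known active Crohn's disease yes; spillage no |
| Dirty | Pus, perforation or abscess | Sometimes suspected; not if unexpected |

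Table 3's own examples show the difficulty. A right hemicolectomy sits in the second class and a colectomy with some spillage in the third. The planned operation alone does not settle the class. The gap is therefore confined mainly to spillage and unexpected findings.

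**2. What the classes imply for risk**

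Table 3 gives infection rates of 1-2%, below 10%, 15-20% and below 40%. Two of these are upper bounds only. The one contrast between neighbours with a guaranteed minimum above 1 is contaminated against clean-contaminated: more than 15/10 = 1.5-fold. Moving patients across that boundary changes the case mix of both classes.

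**3. Can the bias be sized?**

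The documents give no class frequencies and no regrading rates, so the inputs below are assumptions. Both examples assume no true device effect.

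*Example A.* Per 100 patients in each arm: 60 clean-contaminated at 8% and 20 contaminated at 17.5%. Ten of the 60 are recorded one class higher in the device arm only.
- Device-arm rate in the recorded contaminated class: (20 × 0.175 + 10 × 0.08)/30 = 4.3/30 = 14.3%.
- Control-arm rate: 17.5%. Apparent risk ratio 14.3/17.5 = 0.82.
- If the same regrading happens in the control arm instead: 17.5/14.3 = 1.22.

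*Example B.* Per arm: 200 clean-contaminated at rate r1 = 5-8% and 100 contaminated at rate r2 = 15-20%. A share s = 5-20% of device-arm contaminated cases is recorded one class lower. The device-arm rate in the recorded clean-contaminated class is (200 r1 + 100 s r2)/(200 + 100 s).
- Smallest effect (r1 = 8%, r2 = 15%, s = 5%): (16 + 0.75)/205 = 8.17% against 8%, odds ratio 1.02.
- Largest effect (r1 = 5%, r2 = 20%, s = 20%): (10 + 4)/220 = 6.36% against 5%, odds ratio 1.29.

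Apparent benefit or apparent harm follows from which arm is regraded and in which direction. The examples show that a mechanism exists; they do not estimate its size here. With a class recorded before allocation and left unchanged, no regrading by arm can occur.

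**4. Sample size**

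For 12% against 6%, two-sided 0.05 and 80% power, with pooled variance: n = [1.96 √(2 × 0.09 × 0.91) + 0.8416 √(0.12 × 0.88 + 0.06 × 0.94)]² / 0.06² = 356 per arm, against 355 in Table 2. Allowing 5% dropout, 710/0.95 = 748, consistent with 750. No contamination class enters this calculation, so the point does not change it.

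**The case against.** The strongest reply is that an anticipated class was plainly intended. Table 3's title speaks of potential contamination. The Study Design section describes stratification by baseline infection risk. The Randomisation section refers to a notepad of operation-specific details gathered before randomisation; that additional file is not shown, may well ask for an expected class, and cannot be counted as missing. The examples attached to secondary outcome 1 are procedure types, generally known before incision. The primary model does not adjust for contamination at all, and the protocol calls p values other than the primary one nominal.

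Most of this stands. It disposes of two stronger readings that a reader might infer. One is that the stratification cannot work. It can, on an anticipated class, and many cases are predictable. The other is that the contamination subgroup will be biased because an unblinded surgeon records the final class. No shown text says that a final class is recorded, when, or by whom, and the case report forms are in an additional file.

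What the reply does not remove is the mismatch in the shown text. Table 3 still defines classes by operative events, the rationale still speaks of the contamination that results from surgery, and nothing says which version serves secondary outcome 1.

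**Conclusion.** The point holds as a mismatch of definition and timing with an inexpensive remedy. The Table 3 class as defined cannot be the minimisation factor; an expected class can. Whether the contamination subgroup is at risk depends on which version is used, and the protocol article does not say. If the operative class were used, it would be a post-randomisation variable open to grading with knowledge of the arm.

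No figure should be attached to that risk. The apparent ratios above (0.82, 1.22, 1.02 to 1.29) rest wholly on assumed class sizes and regrading rates, and even their direction is set by assumption. A reader might also take Table 3 to show at least a doubling of risk from each class to the next; its upper bounds do not support that. The comparison of the randomised groups as a whole remains valid, and the sample size stands.

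**What to change.** - **Randomisation section:** state that the minimisation factor is the surgeon's expected contamination class, recorded before allocation and not altered afterwards.
- **Secondary outcome 1 and the matching aim in the abstract:** state that this recorded value defines the subgroups.
- **Analysis of Primary and Secondary Outcomes:** add the recorded class as a fixed effect to the primary model, which now names only surgeon random effects, so that the analysis reflects the factor used in allocation.
- **Any final operative class:** report it by arm, cross-tabulated with the expected class, as descriptive or sensitivity information only.

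The first two changes are wording. The third is a change to the analysis: the odds ratio becomes conditional on class and should be described that way. The expected class will predict infection somewhat less well than the final class, so some precision is given up in return for a variable that the allocation cannot influence. Recruitment is unchanged.

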## List of Abbreviations

SSI: Surgical Site Infection; NICE: National Institute for Health and Clinical Excellence; RCT: Randomised Controlled Trial; NHS: National Health Service; CDC: Centers for Disease Control and Prevention; QoL: Quality of Life; QALY: Quality Adjusted Life Year; PI: Principle Investigator; UKCRC: United Kingdom Clinical Research Collaboration; CRF: Case Report Form; BMI: Body Mass Index.
